### **8.2 Secondary end-points**

(1) Stage II or III necrotizing enterocolitis (NEC, Bell standard)

(2) Hospitalization days

(3) Body weight at discharge

(4) Duration of total parenteral nutrition

(5) Cholestasis(Serum binding bilirubin concentration > 1.0 mg/dL (17.1 mmol/L)

Serum total bilirubin < 5.0 mg/dL (85.5 mmol/L) or >20%

Total bilirubin concentration >5.0 mg/dL (85.5 mmol/L), measured 2 weeks after birth in two groups

(6) Any adverse events reported: nosocomial infection, nosocomial death, retinopathy of prematurity (ROP, any stage), chronic lung disease (CLD), requirement of ventilatory support or oxygen after a corrected gestational age of 36 weeks, intraventricular hemorrhage (IVH, grade 2 and above), bronchopulmonary dysplasia (BPD), late-onset sepsis (LOS), diarrhea, colon perforation, malabsorption, rectal bleeding, and rectal trauma.

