## **11. Sample size and statistical power estimation**

The sample size estimate is based on our pilot study; the time of complete meconium evacuation was 1.4 days, 1.2 days, and 1.2 days earlier in the breast milk enema group than in the saline enema group at  $23 \text{ w} \leq \text{gestational age} < 28 \text{ w}$ ,  $28 \text{ w} \leq$

gestational age < 29 w, and 29 w  $\leq$  gestational age < 30 w, respectively. Given that  $\alpha = 0.05$ ,  $\beta = 0.2$ , standard deviation (SD) = 2, sampling ratio = 1 and taking a 20% drop rate into account, the required total sample size is 78, 108, and 108 premature infants in each gestational age, respectively. A website was used to calculate the sample size (<http://powerandsamplesize.com/Calculators/>).

| Gestational age               | Difference | $\alpha$ | $\beta$ | SD | Sample size | Loss of follow-up | Final sample size |
|-------------------------------|------------|----------|---------|----|-------------|-------------------|-------------------|
| 23W $\leq$ Gastinal age < 28W | 1.4d       | 0.05     | 0.2     | 2  | 64          | 20%               | 78                |
| 28W $\leq$ Gastinal age < 29W | 1.2d       | 0.05     | 0.2     | 2  | 88          | 20%               | 108               |
| 29W $\leq$ Gastinal age < 30W | 1.2d       | 0.05     | 0.2     | 2  | 88          | 20%               | 108               |

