#### **14.2 Analysis of Primary Outcomes**

The two primary outcomes include the time to achieve complete meconium evacuation and the time to complete enteral feeding. Outcomes are presented as median (Q1-Q3). The outcomes will be analyzed using an independent sample t-test or Mann–Whitney test. Meanwhile, a multiple linear regression model will be used to analyze the factors affecting primary outcomes, including gender, birth weight, history of a mother's disease, etc. For outcome differences between the treatment and control arms, the median difference and 95% confidence interval (CI) will be assessed using the Mann–Whitney U test and the Hodges–Lehmann method. The time to achieve complete meconium evacuation and full enteral feeding will be analyzed using Kaplan–Meier curves and log-rank tests. In the Kaplan–Meier analysis, the computation of the median time holds significant methodological importance.

Precisely, the median time to accomplish complete meconium evacuation and full enteral feeding are ascertained as the time point at which 50% of the study participants reach these predefined endpoints.

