### **14.3 Analysis of Secondary Outcomes**

The secondary outcomes will include the hospitalisation days, weight at the time of discharge, and duration of TPN. The outcomes will be analyzed using an independent sample t-test or Mann–Whitney test. Meanwhile, a multiple linear regression model will be used to analyze the factors affecting primary outcomes, including gender, birth weight, history of a mother's disease, etc. Outcomes are presented as median (IQR). For outcome differences between the treatment and control arms, the median difference and 95% CI will be assessed using the Mann–Whitney U test and the Hodges–Lehmann method.

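### Sections 14.2 and 14.3 give no rule for infants who die: the stated Kaplan–Meier median is wrong if deaths are censored, and raw durations let an early death enter as a short one

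*Protocol*

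**What the plan says.** Section 14.2 applies several methods to the two primary times. One sentence states: "The time to achieve complete meconium evacuation and full enteral feeding will be analyzed using Kaplan–Meier curves and log-rank tests". The section then defines the resulting median as the "time point at which 50% of the study participants reach these predefined endpoints". The same times are also to be compared by t-test or Mann–Whitney test, with a Hodges–Lehmann interval, and modelled by linear regression. No censoring rule and no rule for death is given.

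Section 14.3 states: "The secondary outcomes will include the hospitalisation days, weight at the time of discharge, and duration of TPN". For these, "The outcomes will be analyzed using an independent sample t-test or Mann–Whitney test", again with a Hodges–Lehmann estimate. Section 14.1 plans intention-to-treat and per-protocol analyses and restricts neither to survivors.

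Death appears only as a harm. Section 8.2 lists "Any adverse events reported: nosocomial infection, nosocomial death" among the adverse events, section 9.2 repeats it, and section 14.4 summarises death descriptively.

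Section 10.3 gives mean imputation and last observation carried forward as examples for missing data, with a complete-case comparison as sensitivity analysis. It does not mention death.

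**The concern.** The infants are of 23 to under 30 weeks' gestation, and the protocol itself lists in-hospital death as an event to record. An infant who dies before full feeding never reaches that endpoint, yet the methods named do not treat the death in that way.

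- Kaplan–Meier with deaths censored estimates when half would have reached the endpoint if deaths were removed and the infants who died would have progressed like the others. That is not the time at which half of the participants reach it.
- The t-test, Mann–Whitney test, Hodges–Lehmann estimate and linear regression need a completed time for each infant. Under section 10.3, mean imputation would give an infant who died an average feeding time, carrying forward has no earlier value of a once-only time to use, and complete-case analysis drops the infant.
- Hospital days and days of parenteral nutrition stop at death. Compared as raw durations, an early death counts as a short one, and short is favourable.

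At stake is the direction of error. An arm with more deaths would carry no penalty on time to full feeding and could appear to have shorter stays.

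**Working it through.** **The plan's own figures.** The protocol derives only a sample size, from the meconium outcome: "the time of complete meconium evacuation was 1.4 days, 1.2 days, and 1.2 days earlier in the breast milk enema group", with "standard deviation (SD) = 2, sampling ratio = 1 and taking a 20% drop rate into account". With two-sided alpha 0.05 and power 0.80, n per arm = 2 × (1.960 + 0.842)² × 2² / d². For d = 1.4 this is 32.0 (total 64.1, or 66 if each arm is rounded up); for d = 1.2 it is 43.6, so 44 per arm and 88 in total. The plan states 64, 88 and 88, which agrees closely. It is used here only for the arm size: 78 + 108 + 108 = 294, so 147 per arm. The plan states no death rate and no expected feeding time or length of stay; all such values below are assumptions.

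**Kaplan–Meier median, closed form.** Let a fraction p die before full feeding, and let F be the distribution of feeding time in the others. The share of all infants who have reached the endpoint by time t is (1 − p)F(t), so the 50% point solves F(t) = 0.5/(1 − p). Assume a lognormal time with median 14 d and log-SD 0.4.

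- p = 0.05: F = 0.526, z = 0.066, t = 14 × exp(0.4 × 0.066) = 14.37 d.
- p = 0.15: F = 0.588, z = 0.223, t = 14 × exp(0.4 × 0.223) = 15.31 d.

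Kaplan–Meier with independent censoring of deaths gives 14.0 d in both cases.

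**The same by simulation** (400,000 infants; lognormal, assumed median 25 d and log-SD 0.35; constant hazard of death):

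| Die before full feeding | Kaplan–Meier median, deaths censored | Time when 50% of all infants have reached it | Median among those who reached it |
|---|---|---|---|
| 0% | 25.0 d | 25.0 d | 25.0 d |
| 2% | 25.0 d | 25.2 d | 25.0 d |
| 5% | 25.0 d | 25.5 d | 24.9 d |
| 10% | 25.0 d | 25.9 d | 24.7 d |
| 20% | 25.0 d | 27.2 d | 24.4 d |
| 30% | 25.0 d | 29.1 d | 24.0 d |

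The third column is what section 14.2 defines. The last column is what a complete-case analysis sees, and it moves the other way.

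**Hospital days, means.** Assume every survivor stays 60 d and every death occurs on day 10. Mortality of 8% gives 0.92 × 60 + 0.08 × 10 = 56.0 d; mortality of 4% gives 0.96 × 60 + 0.04 × 10 = 58.0 d. The arm with twice the deaths has a mean 2.0 d shorter. The planned Hodges–Lehmann estimate is nevertheless 0 here, because 0.92 × 0.96 + 0.08 × 0.04 = 0.886 of the pairwise differences are zero. The 2-day figure therefore belongs to the t-test option only.

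**Hospital days, with spread.** Assume a lognormal stay in survivors, median 60 d and log-SD 0.3 in both arms, deaths uniform over days 1 to 20, 147 per arm and 2,000 simulated trials:

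| Mortality | Hodges–Lehmann difference | Mann–Whitney rejection at 5% |
|---|---|---|
| 5% v 5% | 0.0 d | 5% |
| 5% v 10% | -1.7 d | 11% |
| 5% v 15% | -3.9 d | 30% |
| 10% v 20% | -4.0 d | 32% |

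A negative value favours the arm with more deaths, although survivors' stays are identical. The same mechanism applies to duration of parenteral nutrition, which was not simulated.

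**The case against.** **Most of this is silence.** Section 14.3 does not say that a death's observed stay is entered, and section 14.2 does not say that deaths are censored. A reader might infer that the plan counts deaths as endpoint events, or expressly scores them as short stays. The documents support neither: death is a separate harm throughout and is nowhere counted as reaching an endpoint. A separate analysis plan, not at hand, could hold the rule. This stands in part. However, section 14 is itself headed as the statistical analysis plan, and it fixes the median's definition and the raw-duration tests. A later document would have to replace these, not only add to them.

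**The definition can be right.** If infants who die stay in the risk set as never reaching the endpoint, the sentence in section 14.2 is correct. This stands, and it is the reading that the fix adopts.

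**Withdrawals are not deaths.** Section 15 expects some infants to leave before full feeding. They can still reach it later, and Kaplan–Meier handles such exits properly if they are non-informative. The gap applies only to deaths, so the 20% loss allowance is no guide to its size.

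**No bias between arms is shown.** With equal mortality the stay comparison is unbiased, and any gap in the median is alike in both arms. A reader might infer that the trial's results are biased; that needs unequal mortality, for which the documents give no figure. No size is given for meconium evacuation either.

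**Other analyses are legitimate.** Censoring deaths to compare cause-specific hazards is a recognised method. It may stay, provided that its median is not described as the time at which half of all participants reach the endpoint.

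**Conclusion.** The point holds in this form. The definition in section 14.2 is false for a Kaplan–Meier median with deaths censored, and the other methods listed there have no valid value for an infant who dies first. The size depends on mortality: about 0.2 to 0.9 d at 2% to 10% deaths, under the assumed 25 d feeding median. Section 14.3, applied as written under intention to treat, lets an early death act as a short duration. If mortality differs between arms, this favours the arm with more deaths, by about 1.7 d at 5% v 10% and 3.9 d at 5% v 15% under the stated assumptions, and by nothing at equal mortality. The direction follows from the methods; the magnitudes are illustrative. The rule should be fixed before analysis, because once deaths by arm are known the choice is no longer neutral.

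**What to change.** **Section 14.2.** Treat death before the endpoint as a competing event: the infant never reaches it. Report cumulative incidence by arm for both primary times and read the median from it, so that it matches the stated definition. A log-rank or cause-specific comparison may be kept beside it. In any rank test, give deaths the worst rank. State that the imputation in section 10.3 is not applied to deaths. If the t-test and linear regression are kept, describe them as analyses of infants who reached the endpoint.

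**Section 14.3.** Replace raw hospital days by time to discharge alive, and duration of parenteral nutrition by time to alive and off parenteral nutrition, with death as a competing event or given the worst rank. Show mortality by arm beside these results and beside discharge weight, which should be labelled as a result in survivors.

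**Cost.** Some wording and modest programming. The date of death must be captured: section 9.2 lists in-hospital death without mentioning a date, but the daily follow-up in section 12.8 makes this feasible. The estimates will be slightly less familiar to clinical readers.

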### **14.3 Analysis of Secondary Outcomes**

The secondary outcomes will include the hospitalisation days, weight at the time of discharge, and duration of TPN. The outcomes will be analyzed using an independent sample t-test or Mann–Whitney test. Meanwhile, a multiple linear regression model will be used to analyze the factors affecting primary outcomes, including gender, birth weight, history of a mother's disease, etc. Outcomes are presented as median (IQR). For outcome differences between the treatment and control arms, the median difference and 95% CI will be assessed using the Mann–Whitney U test and the Hodges–Lehmann method.

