## **9.1 Baseline demographic information**

(1) Mother's information: general information (name, age, date of birth, ethnicity, education level, ID number, home address, and contact information), medical history (pregnancy-induced hypertension syndrome and gestational diabetes), use of medicine during pregnancy, infant delivery method, and maternity.

(2) Infant's information: gestational age, sex, birth weight (g), starting time of enteral feeding within 48 hours after birth, method of enteral feeding (breast milk only/breast milk formula mix/formula only), and Apgar score (1 min, 5min).

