### **14.5 Subgroup Analysis**

For all aforementioned statistical analyses, stratified subgroup analyses will be conducted based on gestational age to compare specific intra-group outcomes. Gestational age categories are 23 weeks  $\leq$  gestational age < 28 weeks, 28 weeks  $\leq$  gestational age < 29 weeks and 29weeks  $\leq$  gestational age < 30 weeks This approach is employed to assess nuanced differences within distinct gestational age subgroups, enabling a comprehensive evaluation of outcomes tailored to the developmental stage of the fetus.

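### Section 14.3 carries over the primary-outcome regression sentence and, once that is corrected, still compares discharge weight between arms without using the birth weight that is collected at baseline (minor)

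*Protocol*

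**What the plan says.** Section 14.3 opens with its scope: "The secondary outcomes will include the hospitalisation days, weight at the time of discharge, and duration of TPN". It then makes three statements about method.

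- Test: "The outcomes will be analyzed using an independent sample t-test or Mann–Whitney test".
- Regression: "a multiple linear regression model will be used to analyze the factors affecting primary outcomes, including gender, birth weight", followed by maternal disease history and an open end to the list.
- Estimate of the arm difference: "the median difference and 95% CI will be assessed using the Mann–Whitney U test and the Hodges–Lehmann method".

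Section 14.2, on the primary outcomes, has the same regression sentence: "Meanwhile, a multiple linear regression model will be used to analyze the factors affecting primary outcomes, including gender, birth weight, history of a mother's disease," and so on.

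Three other sections bear on the point. Section 9.1 lists birth weight in grams among the infant baseline data. Section 5 stratifies the randomisation by gestational age. Section 14.5 adds: "For all aforementioned statistical analyses, stratified subgroup analyses will be conducted based on gestational age".

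**The concern.** There are two separate matters.

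The first is textual. The regression sentence stands under the secondary-outcome heading but names the primary outcomes as the response. Followed to the letter, it repeats the regression of Section 14.2 and gives the three secondary outcomes none.

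The second remains after that word is corrected. The sentence describes a search for factors that affect an outcome and does not name treatment arm as a term. The arm difference is assigned elsewhere in the section, to methods that take no covariates. Discharge weight has an obvious baseline counterpart in birth weight. The plan collects it and treats it as prognostic, but does not use it in the arm comparison.

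At stake is the width of the confidence interval for a secondary outcome, and whether the adjusted model is fixed before the data are seen.

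**Working it through.** **Step 1. The two regression sentences side by side.** Sections 14.2 and 14.3 use the same sentence, with the same response (primary outcomes) and the same open list of factors (gender, birth weight, maternal disease history and others). It fits its place in 14.2. In 14.3 it stands between the test and the estimate for the secondary outcomes, and would be redundant if it really meant the primary ones. A carry-over from 14.2 is the natural reading, though the text alone cannot prove it.

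**Step 2. What changes if the word is corrected.**

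| Element of 14.3 | As written | With *secondary* put in |
|---|---|---|
| Test between arms | t-test or Mann–Whitney | the same |
| Arm difference and 95% CI | Hodges–Lehmann | the same |
| Regression response | primary outcomes | secondary outcomes |
| Treatment arm named as a model term | no | no |
| Adjusted arm difference specified | no | no |

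The missing adjustment is therefore not caused by the slip. It comes from how the arm comparison is specified.

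**Step 3. Number of infants.** The protocol gives no sample-size or power figure for a secondary outcome. Section 11 sizes the trial on meconium evacuation alone (SD 2 days, two-sided 0.05, power 80%). As a check on its evaluable numbers, n per arm = 2 × (1.960 + 0.842)² × 2² / difference²:

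- 1.2 days: 2 × 7.85 × 4 / 1.44 = 43.6, so 44 per arm and 88 in total (stated 88).
- 1.4 days: 2 × 7.85 × 4 / 1.96 = 32.04, so 33 per arm and 66 in total if rounded up (stated 64, a rounding matter).

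The planned evaluable total is 64 + 88 + 88 = 240. The recruitment total, 78 + 108 + 108 = 294, includes the allowance for loss, so 240 is the fairer base here.

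**Step 4. Precision given up.** Let r be the within-arm correlation between birth weight and the outcome. Adjusting a mean difference for one baseline covariate in a linear model multiplies its variance by 1 − r² and its CI width by √(1 − r²). The equivalent unadjusted sample is 240 / (1 − r²). The protocol gives no r, so all four values are assumptions.

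| r (assumed) | 1 − r² | √(1 − r²) | CI shorter by | 240 infants act like |
|---|---|---|---|---|
| 0.1 | 0.99 | 0.995 | 0.5% | 242 |
| 0.3 | 0.91 | 0.954 | 5% | 264 |
| 0.5 | 0.75 | 0.866 | 13% | 320 |
| 0.7 | 0.51 | 0.714 | 29% | 471 |

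This compares a linear model with an unadjusted difference in means. The planned interval is Hodges–Lehmann, so the table shows the order of the gain and does not measure the exact change from the planned analysis.

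**Step 5. Whether other parts of the plan supply the adjustment.** Stratified randomisation (Section 5) limits imbalance in birth weight between arms, but birth weight still varies within a gestational-age band. Section 14.5 gives separate results within each band. It does not give one overall difference adjusted for birth weight.

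**The case against.** The strongest reply is that the slip is harmless and the rest is preference. The sentence plainly means the secondary outcomes. Comparing randomised arms without adjustment is legitimate, and Section 14.3 fixes a coherent way to do it. Gestational age enters through both the randomisation and Section 14.5. The factor list is open-ended and does not exclude treatment arm, and a separate SAP may settle the model terms. Section 14.2 has the same features, so if lack of adjustment matters, it matters first for the primary outcomes.

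Most of this stands, and it sets the severity. Three stronger readings that a reader might infer are not supported:

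- *That the wrong word is why the secondary outcomes are compared unadjusted.* Step 2 shows that the arm comparison is the same with either word. Nor does the protocol state a decision to leave these outcomes without regression.
- *That the discharge-weight comparison is biased.* Randomisation protects it. A chance imbalance in birth weight could move the particular estimate obtained, but the unadjusted interval already allows for such chance, and stratification limits it.
- *That a linear model should become the main analysis for all three outcomes.* Section 14.3 plans hospital days and duration of parenteral nutrition as medians with rank-based differences, and nothing in the document shows that a mean-based model suits them better.

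What the reply does not remove is that the section names the wrong outcomes. It also leaves unused, in the discharge-weight comparison, a baseline measurement that the plan already holds and already counts as prognostic. A later SAP could settle this, but only by clarifying or departing from the present text.

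**Conclusion.** The point holds as a minor one, in two parts. Section 14.3 contains a probable carry-over error in the outcome it names. Independently of that, the discharge-weight comparison is valid but less precise than it could be at no cost.

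The gain runs from negligible (0.5% of CI width at r = 0.1) to substantial (29% at r = 0.7) and rests wholly on a correlation that the protocol does not give. It also assumes a linear relation and 240 evaluable infants; the percentages do not depend on that number. No secondary outcome has a stated power target that is lost, and no primary conclusion or sample size is affected. The case is firmest for discharge weight. It is weaker for hospital days and duration of parenteral nutrition, which may be skewed.

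**What to change.** In Section 14.3:

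1. Change *primary* to *secondary* in the regression sentence, and state that the model includes treatment arm.
2. For discharge weight, report the arm difference with its 95% CI from a linear model with treatment arm, birth weight and the gestational-age stratum used for randomisation, alongside the planned unadjusted result.
3. For hospital days and duration of parenteral nutrition, keep the planned rank-based comparison as the main result. Add the adjusted arm difference as supportive, with a check or transformation for skewness.

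The cost is a few sentences of analysis wording and one additional model per outcome. No new data and no more infants are needed, since birth weight and gestational age are already collected.
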